#### Handling of missing data and drop-outs

If outcomes are missing, we will employ multiple imputation in the primary analysis and additionally perform an available case analysis as sensitivity analysis disregarding missing data. The DEMMI score that is measured two times during follow-up will additionally be evaluated in a repeated measures mixed-effects linear model, additionally introducing a random intercept for patients into the model.

#### Interventions

*Experimental group*: In patients assigned to GDM, a trained physiotherapist will provide a short educational intervention on GDM. Further, the physiotherapist will define a personal mobility goal based on an adapted version of the Johns Hopkins Highest Level of Mobility (JH-HLM) scale (table 3, online supplemental figure 1).^11 20^ To avoid a ceiling effect in our population, compared with the original version of the JH-HLM, we added the following mobility goal: ‘Level 8: Walking 75 m or more (30 min or stairs) and no bed rest during daytime’ and skipped the original ‘Level 1: Only lying’.

10.1136/bmjopen-2021-058509.supp2Supplementary data

**Table 3 T3:** Comparison of JH-HLM and GoMob-in mobility goal levels

Level	JH-HLM	GoMob-in mobility goal level
1	Only lying	Bed activities
2	Bed activities	Sit at edge of bed
3	Sit at edge of bed	Transfer to chair/commode
4	Transfer to chair/commode	Standing for >1 min
5	Standing for >1 min	Walking 10+ steps
6	Walking 10+ steps	Walking 7.5 m or more
7	Walking 7.5 m or more	Walking 75 m or more
8	Walking 75 m or more	Walking 75 m or more (30 min or stairs) and no bed rest during daytime

JH-HLM, Johns Hopkins Highest Level of Mobility Scale.

Participants will be instructed that they should aim for successful completion of the task at least three times daily. The mobility goal level will be defined regularly by the treating physiotherapist together with the patient taking into account the current physical activity. Reassessment will serve as opportunity for a short motivational intervention (‘booster session’). The mobility goal level should be increased regularly. In patients reaching the highest mobility goal level, a note will be placed on the bed to indicate the patient to use the bed only for examinations and for sleep. All medical personnel (eg, nurses) caring for the participant are allowed to adapt the mobility goal level. Increasing the mobility goal level more than one step or lowering is also allowed. The study personnel will instruct nurses and physicians caring for participants in the intervention group regularly about the ongoing trial and its aims, that is, responsible resident physicians will be informed by email after randomisation of a participant to the intervention group, nurses will be instructed orally and with leaflets at staff meetings at the beginning of the study and if deemed necessary.

The mobility goal level will be depicted on a patient board next to the bed, visible for all stakeholders (patients, visiting friends and family, physicians, nurses, physiotherapists).

*Control group*: Patients assigned to the control group will receive standard treatment of the GIM wards. Mobility goals will not be routinely set nor encouraged interprofessionally. Patients will receive physiotherapist’s guided training as prescribed by the resident in charge (resident physician/‘Assistenzarzt’). As in any exercise trial, physiotherapists providing the standard treatment cannot be blinded to participation of the patients in the control group. They address the specific needs and provide general non-systematic information about the importance of mobilisation during hospitalisation as part of their routine instruction for all patients.

The adherence to intervention protocol will be assessed by presence of the patient board displaying the mobility goal level at discharge.

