### Primary outcome

The primary outcome will be the change in physical activity level measured by performance in the DEMMI score between baseline and 5 days of follow-up.^28^ Trained study personnel will evaluate physical activity by using DEMMI score at baseline before randomisation, while a physiotherapist blinded to the group allocation will assess DEMMI score 5 days later.

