Sociodemographic and anthropometric data (eg, age, gender, weight and height, zip code (rural versus urban living area), marital status, nurse visit at home (German: Spitex), insurance coverage (private or not), admission mode (elective or urgent), transfer from intensive care unit, hospitalisation in the last 6 months), previous use of mobility aids.Comorbidities will be reported by the participant, using an established, systematic method as previously described.^38^Functional status using Barthel index. The Barthel index is one of the most widely used and reliable functional outcome measures and is measured through an established and validated questionnaire where higher scores on a scale between 0 and 100 indicate greater independence in activities of daily living.^30^ It can be conducted by telephone and a validated German version is available.^31^ If the patient is not able to answer the questions, the Barthel index will be administered by interviewing the ward nurse caring for the patient, a family member or any other person caring for the patient before hospitalisation (eg, home care nurse).Concerns of falling using FES-I. FES-I is a validated 16-item tool to evaluate concerns of falling, with 16 score points indicating no concerns of falling and 64 score points indicating high levels of concern.^32^ It can be conducted by telephone and a validated German version is available.^33^Quality of life will be assessed with the EQ-5D-5L questionnaire. The EQ-5D-5L^34 35^ is an established, standardised measure of quality of life consisting of a descriptive system compromising the five dimensions mobility, self-care, usual activities, pain/discomfort and anxiety/depression with five levels each (no problems, slight problems, moderate problems, severe problems, and extreme problems) and a visual analogue scale with 0 indicating the worst health and 100 indicating the best health.^39^ It can be conducted by telephone interview and a validated German version is available.^36^Physical activity will be assessed by a trained study nurse using the DEMMI score. The German version of the DEMMI is a valid^40^ and reliable^39^ instrument to measure physical activity in older adults in the acute hospital setting and has no floor or ceiling effect.^28 37 41^ Based on 15 items (0–19 points with Rasch conversion to a score ranging from 0 (indicating poor physical activity) to 100 (indicating a high level of independent physical activity)), the DEMMI includes evaluation of movement in bed (three items), chair (three), static balance (four), walking (two) and dynamic balance (three). Acute older adult patients with a DEMMI score below 41 score points had significantly lower Barthel index (38% vs 79%), used more mobility aids, were more bedridden, longer hospitalised and were more often discharged to rehabilitation compared with those with a higher DEMMI score.^42^ No association was found for gender, age, weight, body mass index, Charlson comorbidity index or handgrip strength.^42^ Trained personnel is able to complete the DEMMI in no more than 10 min.

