#### Blinding

The DEMMI will be assessed by an independent physiotherapist not otherwise involved in the treatment of patients on the ward and to whom the group allocation of the participant is not declared. The patient will be instructed to not reveal the group allocation to the DEMMI assessor.

The statistician responsible for the final analysis will have no access to the group allocation until the primary analysis of the trial is finished. The data analysis will be conducted according to a prespecified statistical analysis plan.

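### Blinding of the DEMMI assessor is not protected against the bedside goal board and bed note, which mark the intervention arm, and is likely to be broken at follow-up

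*Protocol article*

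**What the plan says.** **The claim.** The Abstract, the strengths list and Study setting all describe outcome assessment as blinded. Under Primary outcome, "a physiotherapist blinded to the group allocation will assess DEMMI score 5 days later".

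**The safeguards.** The Blinding section describes an independent physiotherapist who does not otherwise treat patients on the ward, "to whom the group allocation of the participant is not declared". It adds: "The patient will be instructed to not reveal the group allocation to the DEMMI assessor".

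**The visible markers.** Under Interventions, for the experimental group: "The mobility goal level will be depicted on a patient board next to the bed, visible for all stakeholders". The list of stakeholders that follows includes physiotherapists. For patients who reach the top goal level, "a note will be placed on the bed to indicate the patient to use the bed only for examinations and for sleep". Controls get standard treatment without routine goal setting, and no board is described for them. Adherence is judged by "presence of the patient board displaying the mobility goal level at discharge".

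**The assessment.** Under Baseline assessment, the DEMMI has 15 items, three of them movements in bed. Under Follow-up, it is repeated on day 5 and again at discharge or day 14, whichever is earlier. A footnote to Table 2 drops the day-5 visit if the discharge visit falls before day 6.

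**The concern.** The board identifies the arm. It hangs only at intervention beds and also shows the goal the patient is working towards. Both safeguards deal with the assessor being told the allocation; neither deals with the assessor seeing it. An assessor who reads the board before or during the test knows the arm.

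The DEMMI is scored by an observer. Knowledge of the arm can tilt borderline item scores, most plausibly towards the intervention. The day-5 primary outcome is exposed, and so are the discharge/day-14 DEMMI and the secondary outcome of reaching the 9-point minimal clinically important difference. The baseline DEMMI is done before randomisation and is not affected.

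None of the listed analyses would reveal or correct such a tilt. The multiple-imputation, available-case, per-protocol and mixed-model analyses all use the same ratings.

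**Working it through.** **Step 1: does the text protect the assessor from the markers?**

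| Route to unblinding | Safeguard in the article |
|---|---|
| Staff tell the assessor | Allocation not declared |
| Patient tells the assessor | Patient asked not to |
| Assessor sees the board by the bed | None stated |
| Assessor sees the note on the bed (top goal level only) | None stated |

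**Step 2: is the assessor likely to see them?** The place of assessment is not given, so this is inference.
- Three items need a bed, and both follow-up assessments fall during the stay or on the day of discharge. The patient's own bed is the natural place.
- The adherence measure expects the board to be up at discharge, so it should also be up on day 5.
- The exclusion criteria bar a second participant in the same room, so a goal board in the room points to this patient.
- If discharge comes before day 6, the discharge DEMMI is the only follow-up DEMMI, and it falls on the day the board is expected to be present.

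**Step 3: reproduce the plan's sample size.** Inputs from Estimated sample size and power: difference 5, SD 10, two-sided alpha 0.05, power 0.80, drop-out 20%.
- Normal approximation: n = 2 × (1.960 + 0.842)² × 10² / 5² = 62.8, so 63 per arm. The t-based calculation gives 64 per arm (power 0.801), which is the plan's figure.
- Drop-out: 128 / (1 − 0.20) = 160, as stated.

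**Step 4: what an assumed rating bias would do when there is no true effect.**
- SE of the difference = 10 × √(2/64) = 1.77 points.
- Smallest significant difference = 1.96 × 1.77 = 3.46 points.
- For a bias b towards the intervention, the rejection rate = Φ(b/SE − 1.96) + Φ(−b/SE − 1.96).

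| Assumed bias b (points) | b/SE | False-positive rate | Share of the 5-point target |
|---|---|---|---|
| 0 | 0 | 5.0% | 0% |
| 1 | 0.57 | 8.7% | 20% |
| 2 | 1.13 | 20.5% | 40% |
| 3 | 1.70 | 39.6% | 60% |

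**Step 5: what such a bias means in ratings.** The raw scale runs from 0 to 19 and is converted to 0–100. If the conversion were even (an assumption, since it is a Rasch conversion), one raw point would be 100/19 = 5.26 points. A mean bias of 1, 2 or 3 points then equals one extra raw point in about 19%, 38% or 57% of intervention patients (1/5.26, 2/5.26, 3/5.26). These rates show scale only; the document gives no rate of mis-scoring.

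**The case against.** **Location and silence.** The article does not say where the DEMMI is done. Bed items need a bed, but not necessarily the patient's own bed with the board in view. Covering a board during a ten-minute test is the kind of working instruction a journal article can leave to the full protocol, which is not at hand. This stands as far as certainty goes: a reader might infer that the primary outcome is in fact unblinded, and the text does not establish that. It does not remove the point. The article has its own Blinding section with named measures, and those measures do not meet a feature that its Interventions section makes deliberately conspicuous.

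**Who the board is for.** The listed stakeholders are those around the patient's care, and the assessor is defined as outside ward treatment. That is fair: the board is not stated to be meant for the assessor. Still, a board placed to be seen by everyone at the bed will be seen by an assessor at the bed.

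**The adherence check.** A reader might infer that it always coincides with the last DEMMI, or that the assessor performs it. Neither is supported. For stays beyond day 14 the last DEMMI comes before discharge, and the article does not say who checks the board. The check shows only that the board is expected to stay up.

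**The bed note.** It concerns only patients at the highest goal level. The board is the general problem.

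**Size of bias.** The document calls the DEMMI reliable and based on performance, and it gives no evidence of biased scoring. This stands: the bias sizes above are assumptions. The admitted limits on blinding (the interventions and some outcomes) do not settle the matter, because the DEMMI is not named there and is claimed as blinded elsewhere.

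**Conclusion.** The point holds as a conflict between the Interventions and Blinding sections. The assessor is protected from being told the allocation but not from seeing it, and blinding is likely to be broken for the day-5 DEMMI and for the discharge/day-14 DEMMI and minimal-clinically-important-difference outcomes. The likelihood rests on one inference, that follow-up assessments take place at or near the patient's own bed.

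The actual bias is unknown and may be small. The range of about 9% to 40% for the false-positive rate rests on an assumed bias of 1 to 3 points in one direction, 64 per arm and the plan's SD of 10. The planned model adjusts for baseline; if that brings the residual SD below 10, the same bias would give higher rates. The sample size is reproduced and need not change.

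It would go too far to say that the primary outcome is unblinded or that the result will be biased. The documents support only that the blinding claim is unprotected against these markers.

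**What to change.** Add to the Blinding section that existing ward or study staff, other than the DEMMI assessor, cover or remove the goal board and any bed note before every follow-up DEMMI and restore them afterwards. Stating that follow-up DEMMIs are done away from the patient's bed area would serve equally well. Restoring the board keeps the adherence measure at discharge intact.

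Have the assessor record a guess of the allocation after each follow-up DEMMI, and report these guesses by arm with the primary result.

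If the full protocol already contains such a measure, state it in the Blinding section. If none can be put in place, or for assessments made before it was, qualify the blinding claim in the Abstract, the strengths list and the final report.

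The cost is a working instruction, a few minutes per assessment and one extra form field.

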#### Follow-up

Nurses will record falls in the electronic health record (EHR). Hospital parameters, for example, discharge destination, end of hospitalisation, LOS will be collected from the EHR at discharge. Medical data, for example, number of falls and delirium episodes during hospitalisation, main diagnosis and comorbidities will be systematically collected from the discharge letter.

Physical activity will be assessed using DEMMI in all participants on day 5 after study inclusion and on the day of discharge or day 14 (whichever occurs first).

Three months after study inclusion, all participants will be inquired by telephone interview for Barthel index, FES-I, EQ-5D, number of falls since study inclusion (with/without injuries), current destination, rehospitalisations and all-cause mortality. If the patient cannot be reached, a family member or the treating general practitioner will be called to complement data. The patient will be asked to send the falls calendar to the study team. If discrepancy is noted compared with the phone interview, the participant will be called for validation.

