**Trial registration number:**

NCT04760392.

Strengths and limitations of this studyThis is the first study evaluating goal-directed mobilisation in hospitalised general internal medicine patients using blinded outcome assessment.The primary endpoint physical activity will be assessed by change in the de Morton Mobility Index score between baseline and day 5, a reliable tool without floor or ceiling effects.Activity will be recorded by an accelerometer to record the effect of the intervention.The study will also assess independence during activities of daily living, quality of life, number of rehospitalisations and all-cause mortality at 3 months follow-up.The study design is limited by the fact that blinding is not feasible for the interventions and some outcomes.

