### Secondary outcome

Change in DEMMI score between baseline at study inclusion and discharge. Patients hospitalised for more than 2 weeks on GIM wards will be assessed on day 14 after study inclusion instead of at hospital discharge.Percentage of time moving between study inclusion and day 5. Activity will be measured using an accelerometer (GENEActiv, Activinsights, Kimbolton, Cambridgeshire, UK) validated to assess activity in the hospital setting.^13 14 29^Percentage of mobilisation time between baseline and discharge or at 14 days (whichever occurs first).Number of in-hospital delirium episodes (follow-up max. 14 days).Number of in-hospital falls (follow-up max. 14 days)LOS defined as days between hospital admission and discharge.Total number of falls (with/without injuries) within 3 months after study inclusion.Number of rehospitalisations and all-cause mortality within 3 months after study inclusion.Change in independence during activities of daily living (Barthel index) between baseline and 3 months after study inclusion.^30 31^Change in Falls Efficacy Scale-International (FES-I) between baseline and 3 months after study inclusion.^32 33^Change in quality of life (EQ-5D-5L) (visual analogue scale (EQ-VAS) and mobility dimension) between baseline and 3 months after study inclusion.^34–36^Discharge destination (death, acute care hospital, rehabilitation, home, nursing home).Reaching the minimal clinically important difference (MCID) of a change in DEMMI score (9 points) between baseline and discharge.^28 37^

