
**Table 2 T2:** Summary of study procedures based on SPIRIT schedule

	First visit	Second visit*	Third visit	Phone call
Time points (days after randomisation)	0	5	At discharge†	90
Oral and written patient information	+			
Written consent	+			
Inclusion/exclusion criteria	+			
Physical activity (de Morton Mobility Index)	+	+	+	
Randomisation	+			
Demographics	+			
Installation of accelerometer	+			
Read-out of accelerometer			+	
Number of in-hospital falls			+ / daily	
Delirium episodes (EHR)			+	
Length of stay (EHR)			+	
Medical history (EHR)			+	
Destination (EHR)			+	+
Concerns of falling (FES-I)	+			+
Independence during activities of daily living (Barthel-Index)	+			+
Quality of life (EQ-5D)	+			+
Number of falls (with/without injuries)				+
Number of rehospitalisations				+
Mortality				+

*Omitted if third visit before day 6.

†Latest on day 14.

EHR, electronic health record; FES-I, Falls Efficacy Scale-International; SPIRIT, Standard Protocol Items: Recommendations for Interventional Trials.

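### In-hospital falls and delirium are to be counted from the discharge letter, a whole-stay summary that fits neither the EHR recording named elsewhere nor the 14-day limit

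*Protocol article*

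**What the plan says.** Four places in the protocol article bear on these two secondary outcomes.

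- **Follow-up, first sentence.** "Nurses will record falls in the electronic health record (EHR"). Discharge destination, end of hospitalisation and length of stay are then also taken from the EHR.
- **Follow-up, next sentence on data sources.** The "number of falls and delirium episodes during hospitalisation, main diagnosis and comorbidities will be systematically collected from the discharge letter". No 14-day limit is repeated here.
- **Table 2 (schedule).** In-hospital falls are marked at the third visit and as daily; the row names neither a source nor a recorder. Delirium is listed as "Delirium episodes (EHR"), collected at the third visit, which is held no later than day 14.
- **Secondary outcome.** "Number of in-hospital delirium episodes (follow-up max. 14 days") and "Number of in-hospital falls (follow-up max. 14 days").

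On who knows the allocation, the Interventions section says that "responsible resident physicians will be informed by email after randomisation of a participant to the intervention group", and that "The mobility goal level will be depicted on a patient board next to the bed, visible for all stakeholders". Blinded assessment is described only for the DEMMI and for the statistician. The strengths and limitations list concedes that "blinding is not feasible for the interventions and some outcomes".

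**The concern.** A discharge letter is a selective account of a hospital stay. A fall without consequences, or a short delirium episode, may be charted on the ward and never reach the letter. For falls, the plan creates a record at the time of the event and then counts from a summary written later.

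The scope also differs. The letter is to supply events during the hospitalisation, whereas the outcomes are limited to at most 14 days of follow-up, which I read as starting at inclusion. A count made as the Follow-up section is written can therefore include events from before randomisation, which the intervention cannot have influenced, and events after day 14.

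Two extractors, one following the Follow-up text and the other following Table 2, could reach different counts for the same patient. At stake are two listed secondary outcomes that form part of the trial's rationale: the Introduction cites falls and delirium among the harms of immobility. If few events occur, losing some of them makes an apparent absence of difference hard to interpret.

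**Working it through.** **The plan's own figure.** The plan states no figure for falls or delirium. Its only calculation concerns the DEMMI change, and it reproduces. The normal approximation gives 2 × (1.96 + 0.84)² × 10² / 5² ≈ 63 per arm; the t-based calculation gives 64 (power 0.801); 128 / 0.8 = 160. Nothing below affects it.

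**Sources side by side.**

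| Outcome | Follow-up text | Table 2 | Window (Secondary outcome) |
|---|---|---|---|
| In-hospital falls | recorded by nurses in the EHR; counted from the letter | third visit and daily, no source named | at most 14 days |
| Delirium episodes | counted from the letter | EHR, third visit (day 14 at the latest) | at most 14 days |

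For falls, the place of recording and the place of counting differ within one section. For delirium, text and table name different sources, unless the letter is regarded as part of the EHR. For a patient still in hospital on day 14, a discharge letter would not normally exist at the visit where Table 2 schedules the delirium count.

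**Window, late end.** With a constant event rate and a stay of L days from inclusion, the share of events after day 14 is (L − 14) / L, or zero if L ≤ 14:
- L = 14 or less: 0%
- L = 16: 2/16 = 12.5%
- L = 20: 6/20 = 30%
- L = 28: 14/28 = 50%

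This end of the window matters only for long stays.

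**Window, early end.** Patients may enter up to the second day after admission, so events in that short interval can be counted whatever the length of stay. Randomisation balances them on average between arms, but they add noise and dilute any effect.

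**Incomplete capture, equal in both arms (assumed rates).** Take 0.1 falls per patient, 80 patients per arm and Poisson counts with E events in each arm. The 95% CI factor for the rate ratio is exp(1.96 × √(2/E)).
- Full capture: E = 80 × 0.1 = 8.0; factor exp(1.96 × √(2/8.0)) = 2.66
- 60% capture: E = 8.0 × 0.6 = 4.8; factor exp(1.96 × √(2/4.8)) = 3.54

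The rate ratio stays unbiased, but precision is lost.

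**Incomplete capture, unequal between arms (assumed rates).** Observed ratio = true ratio × (capture in intervention / capture in control). With a true ratio of 1.0:
- 80% against 60%: 0.80 / 0.60 = 1.33
- 60% against 80%: 0.60 / 0.80 = 0.75

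These results only restate the assumed capture ratios. They show that the error could go either way, not that it occurs.

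**The case against.** **Arm bias.** A reader might infer that the letter biases the counts by arm, since residents are emailed only about intervention patients. The documents do not support that as a conclusion. They do not say who writes the letter, and the direction of any effect is unknown. Nor is the problem peculiar to the letter: nurses and physicians can all see the goal board, so EHR entries also come from unblinded staff. The limitations list already discloses unblinded outcomes. This objection stands: differential recording is a possibility that the fix does not remove.

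**Impossible window.** A reader might also infer that the 14-day window cannot be followed from a letter, whereas EHR entries are dated and made daily by nurses. The article says neither. Letters may give dates, no passage states that EHR entries are dated, and the daily mark in Table 2 names no recorder. What can be said is that a whole-stay source may not follow the window reliably.

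**No real conflict.** Table 2 also labels medical history as an EHR item, while the Follow-up text takes main diagnosis and comorbidities from the letter. The label may therefore include the letter. This weakens the delirium conflict. It does not settle it, because the Follow-up text names the EHR and the letter as separate sources in consecutive sentences. It also leaves the falls count untouched.

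**Limited importance.** Falls are one secondary outcome among many; the article does not call them the main safety outcome, and safety is handled by serious adverse event reporting. The three-month interview and falls calendar also cover falls since inclusion. That is a partial safeguard, but it serves the three-month total and not the separate in-hospital count.

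**Condensed article.** Extraction details may well sit in the full protocol. The data source, however, is stated here, and the point concerns that statement.

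**Conclusion.** The point holds as a minor improvement to two secondary outcomes. As written, the Follow-up section counts in-hospital falls and delirium from a summary document, although nurses already record falls in the EHR and the schedule labels delirium as an EHR item. The whole-stay scope of that document does not match the 14-day limit.

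The likely consequences are some missed events, some pre-inclusion events counted, and post-window events for patients who stay beyond day 14. How many cannot be told from the documents: every event rate and capture rate used above is an assumption. The conclusion further assumes that ward entries are more complete than the letter and can be placed in time. Both are reasonable, but neither is stated.

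No bias by arm is shown. The primary outcome, its analysis and the sample size of 160 are unaffected.

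**What to change.** 1. Name one source per outcome, in the same terms in the Follow-up section and Table 2: the nurses' EHR entries for in-hospital falls and EHR documentation for delirium episodes.
2. State the counting window there: from randomisation to discharge or day 14, whichever comes first, in line with the Secondary outcome section.
3. Have events extracted by someone unaware of the allocation, where feasible.
4. Keep the discharge letter only as a cross-check for these two outcomes.

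The cost is a rewording and somewhat more extraction time than reading a letter. For falls, the plan already has the record made. The change does not blind the ward staff who record the events, so the trial report should still name that limitation for both outcomes.
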